### Hypotheses

Subjects who receive standard care plus PERT after surgery will demonstrate: 1) symmetrical knee joint loading, 2) symmetrical movement patterns, 3) improved clinical and functional outcomes and 4) improved knee function compared to subjects who receive standard care. Additionally, subjects who receive standard care plus PERT will have a higher return to pre-injury level rates in the short to medium term (6 months -2 years) compared to subjects who receive standard care.

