### Participants

Eighty level 1 and 2 athletes (40 men, 40 women) between the ages of 13 and 55 that have undergone an isolated, unilateral ACL reconstruction will be recruited for this study. Recruiting will be done primarily through the University of Delaware Physical Therapy Clinic. Additional recruitment will consist of newspaper advertisements as well as speaking with local surgeons and rehabilitations specialists. Athletes will be eligible for study enrollment if they were participants in level 1 or 2 activities [1] ≥ 50 hrs/year at the time of their injury, plan to return to their pre-injury level of activity, are ≥ 12 weeks after surgery, demonstrate ≥ 80% quadriceps strength index and minimal knee joint effusion [41].

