### Randomization and allocation concealment

Enrolled subjects will be randomized to a perturbation treatment group (PERT) or a standard treatment group (STND). A statistical random number generator will be used to generate a randomization list, stratified by gender in which an equal number of female and male subjects will be assigned to each treatment group. The research coordinator will generically label the treatment assignments to group A and B to ensure blinding is maintained. This is a single-blinded study in that individuals collecting, recording and analyzing these data will be blinded to group assignment along with the primary investigator and biostatistician. Both the treating physical therapist and the patient will not be blinded to group assignment.

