### Sample size

Minimal clinically importance differences (MCID) for sagittal plane gait variables have previously been established [18]. A power analysis with β = 0.20, α = 0.05 and a medium effect size (0.3) determined that 72 subjects would be needed to detect differences between groups based on MCID’s. To account for a 10% patient drop out a total of 80 subjects will be enrolled in this study. Forty patients will be in each group dichotomized by gender.

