### Data and statistical analysis

Differences between groups will be analyzed using an analysis of covariance (ANCOVA) for biomechanical gait measures and an analysis of variance (ANOVA) will be used for clinical variables. Group assignment will be blinded to the researcher using A and B variables. Assumptions of ANOVA testing will be confirmed prior to statistical analysis. Training group randomization will be used as the between-subjects factor with a within-subjects factor of time. A significance level of p < 0.05 will be set a priori.

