## Discussion

Both short and long term outcomes after ACLR are poorer than previously reported in high-level athletes [1-5]. The explanation of these low return to sports rates appears to be multi-factorial, but may be heavily influenced by lower perceived level of knee function and fear of re-injury [37,53,54]. The relationship of physical performance measures to these subjective evaluations and perceptions of ability are unknown. The aim of this project is to compare the outcomes of two different return to sport training programs in order to establish best-practice guidelines for this high-risk population.

Initial ACL injury rates continue to be elevated and subsequent re-injury rates are even higher despite the positive evolution of post-operative rehabilitation protocols [4,23-28]. Quadriceps weakness, abnormal movement patterns and decreased knee function persist after athletes have returned to sports, supporting the need for a bilateral, neuromuscular training program to promote improved outcomes after ACLR [4,9-17]. Our program was compiled from the latest evidence emphasizing prevention exercises, quadriceps strengthening and perturbation training as a plausible mechanism by which clinicians can maximize post-operative function and reduce second ACL injury risk.

Our study is the first randomized control trial to evaluate the effects of a post-operative intervention program on joint loading, gait biomechanics and clinical outcome measures. Implementing this program in our physical therapy clinic with therapists who have years of expertise executing research protocols allows us to make this post-operative training program generalizable to clinical practice while maintaining the rigor of scientific research. Our subjects will represent several different orthopedic surgeons with a variety of graft types which will allow us to evaluate additional factors outside of our rehabilitation protocol. Our criterion to implement training is based on an array of evidence based clinical measures rather than time based measures (i.e. 6 months) or surgical findings (i.e. bone bruise, meniscus repair) [29,30,38,55]. Group randomization by gender will ensure that effects of treatment are adequately captured. Blinding of researchers collecting these data allows for unbiased reporting of results.

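### Gender stratifies the randomisation but is not named in the analysis model, which can cost precision in between-group comparisons

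*Protocol article*

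**What the plan says.** All references are to the protocol article.

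- **Design.** Randomization and allocation concealment describes a list "stratified by gender in which an equal number of female and male subjects will be assigned to each treatment group". Participants sets 40 men and 40 women. Sample size adds: "Forty patients will be in each group dichotomized by gender". Together these imply 20 men and 20 women per arm.
- **Model.** Data and statistical analysis foresees an "analysis of covariance (ANCOVA) for biomechanical gait measures and an analysis of variance (ANOVA) will be used for clinical variables". It then gives the factors: "Training group randomization will be used as the between-subjects factor with a within-subjects factor of time". Gender is not mentioned there, and the covariates of the ANCOVA are not listed.
- **Testing level.** "A significance level of p < 0.05 will be set a priori". The article does not say whether tests are one- or two-sided.
- **Aims.** The hypotheses compare the two training groups ("Subjects who receive standard care plus PERT after surgery will demonstrate" and so on) and name no gender-specific effect.

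**The concern.** A design that forces gender to balance removes gender differences from the comparison of the arms. If the model then leaves gender out, the same differences stay in the residual variance. The estimated standard error describes a design without stratification and is larger than the true one, so confidence intervals are too wide and power is given away.

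This is more than detail left to a fuller document, because the article does list its factors and the one it stratified on is not among them. The gap is clearest for the clinical variables (quadriceps index, hop tests, patient-reported scores). These belong to the primary outcomes and are assigned an ANOVA, for which no covariates are foreseen.

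The Background gives some reason to expect gender to be prognostic. It reports gender differences in second injury, in attempts to return to sport and in fear during athletic participation, and fear is measured in this trial.

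**Working it through.** **The plan's own numbers.** 72 / (1 − 0.10) = 80 enrolled, and 80 / 2 arms / 2 genders = 20 per cell, so the stated design is balanced. The figure of 72 is reached only with choices that the text does not state. For example, reading the effect size of 0.3 as Cohen's f gives 72 with a one-sided t-test and 90 with a two-sided one. That is a separate matter, and naming gender in the model does not change 72 or 80.

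**Inputs.** N = 72 evaluable and equal cells come from the article. A two-sided alpha of 0.05 is assumed, since sidedness is not stated. R² is the share of outcome variance explained by gender. The article does not give it, so a range is shown. Where other covariates are in the model, R² is the share gender explains beyond them.

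**Between-group contrast (one time point, or the average over time).** With total outcome SD σ and balanced cells:

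- Standard error reported without gender: 2σ/√N
- True standard error: 2σ√(1 − R²)/√N
- Ratio, and so the excess CI width: 1/√(1 − R²) − 1
- Actual alpha: 2[1 − Φ(1.96/√(1 − R²))]

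Example at R² = 0.20: 1/√0.80 = 1.118, so the CI is 11.8% too wide. The critical value becomes 1.96 × 1.118 = 2.191, and the alpha is 0.028.

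For power, take an effect with a nominal 80% (2.8016 reported standard errors). Without gender, power is Φ((2.8016 − 1.96)/√(1 − R²)). With gender it is Φ(2.8016/√(1 − R²) − 1.96).

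| Assumed R² | CI too wide by | Actual alpha | Power without gender | Power with gender |
|---|---|---|---|---|
| 0 | 0% | 0.050 | 0.800 | 0.800 |
| 0.01 | 0.5% | 0.049 | 0.801 | 0.804 |
| 0.05 | 2.6% | 0.044 | 0.806 | 0.820 |
| 0.10 | 5.4% | 0.039 | 0.812 | 0.840 |
| 0.20 | 11.8% | 0.028 | 0.827 | 0.879 |
| 0.30 | 19.5% | 0.019 | 0.843 | 0.918 |

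**Check by simulation.** The settings were N = 72, 40,000 replicates and a correlation of 0.5 between two time points within gender. At R² = 0.20, the follow-up comparison had a mean standard error of 0.235 and alpha of 0.029 without gender, and 0.210 and 0.050 with it. This agrees with the formula.

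**Group-by-time contrast.** If gender shifts every time point by the same amount, the shift cancels in each participant's change. In the same simulation at R² = 0.20, the standard error of the change comparison was 0.210 with or without gender, and alpha was 0.053 both ways. The table therefore does not apply to this contrast. A loss arises there only if gender also changes the time course.

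**Group × gender interaction.** At N = 72 and 80% power, the detectable standardised main effect is 2.8016 × 2/√72 = 0.66. The detectable interaction is 2.8016 × 4/√72 = 1.32, twice as large.

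**The case against.** The strongest reply has four parts.

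1. **The gait ANCOVA may already include gender.** An ANCOVA has at least one covariate, the article lists none, and a covariate list is commonly left to the full protocol or analysis plan. This stands. A reader might infer that gender is missing from every model, but the article supports that only for the stated ANOVA. For the ANCOVA, the most that can be said is that gender is not named.
2. **A treatment effect on change is tested by group × time, where a constant gender difference cancels.** This stands for that contrast. It does not remove the point, because the analysis section sets out to analyse differences between groups, and comparisons at a given time point or on the average over time remain exposed.
3. **Gender may explain little of the variance.** Several primary measures are limb-symmetry indices or between-limb comparisons, so a small R² is plausible and the loss trivial. This stands as a limit on size. Other measures, such as compartment contact forces and patient-reported scores, are not ratios between limbs, and a small R² cannot be assumed for them.
4. **No gender question is left unanswered.** The Discussion says "Group randomization by gender will ensure that effects of treatment are adequately captured", and a reader might infer a promise of gender-specific treatment effects that the analysis fails to deliver. The text does not support this: the words about gender describe how patients are randomised, and neither the purpose nor the hypotheses contain a gender-specific comparison. A group × gender analysis is therefore not owed.

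**Conclusion.** The mismatch between design and stated analysis is real for the ANOVA of the clinical variables and unresolved for the gait ANCOVA. It concerns precision, not validity: the treatment estimate is unbiased and false positives are not increased.

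The loss in between-group contrasts runs from nil (gender unrelated to the outcome) to a CI 19.5% too wide and an actual alpha of 0.019 (gender explaining 30% of the variance). These figures rest on an assumed R², on gender balance holding among those analysed, and on two-sided testing at 0.05. They do not extend to the group-by-time contrast unless gender alters the time course. It would go too far to say that the trial's intervals are wrong in general. The change is still worth making, since it costs almost nothing and the article gives no reason for leaving the stratifier out.

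**What to change.** State in Data and statistical analysis that gender, the stratification factor, enters every ANOVA and ANCOVA as a between-subjects factor, with gender × time added in the repeated-measures models. Settling this before the data are analysed also prevents a later choice between adjusted and unadjusted results.

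The cost is one between-subjects degree of freedom for gender and, with four time points, 4 − 1 = 3 for gender × time. No new data are needed and the sample size does not change.

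Optionally, report a group × gender estimate with its 95% CI, labelled exploratory. No hypothesis calls for it, and at N = 72 it would have low power.

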## Background

Anterior cruciate ligament reconstruction (ACLR) is standard practice for individuals that desire to return to high-level activities, but excellent outcomes are not as commonplace as previously reported [1-5]. Currently, success after ACLR is measured using return-to-sport rates, but second ACL injuries are not only common, but devastating, and have worse outcomes than primary ACLR [6-8]. Quadriceps weakness [9-11], abnormal movement patterns [4,12-16] and below normal knee function [17] are characteristic of athletes in the months following ACLR and often persist up to two years in spite of extensive rehabilitation. Neuromuscular training focusing on restoring limb symmetry and improving knee function using sports-related movements may reduce aberrant movement patterns which are predictive of second injury risk [4,12,18,19].

Risk of a second ACL injury is highest during the first year that athletes return to sports after primary ACL reconstruction [4,13,20-22]. Young females are 16 times more likely to sustain a second ACL injury after primary ACLR and the amount of participation time in high-level activities further increases this risk [23]. Risk to the contralateral limb is higher (5-24%) than the operated limb (4-15%) [4,23-28], suggesting deficits of the involved limb are not exclusively related to re-injury. Altered neuromuscular and biomechanical movement patterns are present bilaterally in response to injury and reconstruction which fails to resolve with post-operative rehabilitation. A neuromuscular training program focused on maximizing performance after ACLR may reduce the risk of a second ACL injury.

Despite current evidence-based post-operative guidelines [29-32], quadriceps strength deficits [9-11], altered biomechanics [4,13-16,33] and poor knee function [17] are reported six months and one year after surgery. International Knee Documentation Committee 2000 subjective knee form (IKDC 2000) scores continue to improve up to one year after surgery suggesting optimal knee function has not been met [17]. Despite clearance for return to sport activities by surgeons and rehabilitation specialists, quadriceps strength deficits of the involved limb compared to the uninvolved limb still exist, and movement asymmetries continue to persist [10,11,14,16].

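### With time as a within-subjects factor, classical ANOVA/ANCOVA in its usual form keeps only patients tested at every visit; a mixed model would use all observed visits

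*Protocol article*

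**What the plan says.** Under *Data and statistical analysis*, the protocol article names "an analysis of covariance (ANCOVA) for biomechanical gait measures and an analysis of variance (ANOVA) will be used for clinical variables". It then sets the model factors: "Training group randomization will be used as the between-subjects factor with a within-subjects factor of time". It does not list the levels of the time factor or the ANCOVA covariate.

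*Procedure* and *Interventions* give four test times: before training, after the 10 sessions, and 1 and 2 years after surgery.

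*Sample size* concludes that "72 subjects would be needed to detect differences between groups based on MCID’s", and continues: "To account for a 10% patient drop out a total of 80 subjects will be enrolled in this study". It does not say what counts as dropout.

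Two other places bear on the later visits. *Outcomes measures* expresses quadriceps strength and hop performance as indices of the involved against the uninvolved limb. The *Background* says, of second ACL injuries: "Risk to the contralateral limb is higher (5-24%) than the operated limb (4-15" (the second range is also in per cent). *Secondary outcome measures* follows re-injury as an outcome at 1 and 2 years.

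**The concern.** A classical analysis of variance with a within-subjects time factor needs a value at every level of time for each patient. In its usual software form it removes any patient with a gap. Over four visits spread across two years, a patient who attends baseline and post-training but misses the 2-year test would contribute nothing, not even to the comparison at the end of training.

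Two things are at stake. The analysed number can fall below the planned 72 although the data for the earlier comparison were collected. The analysed patients would also be those who kept every appointment, rather than those who were randomised.

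A related measurement issue arises at 1 and 2 years even when attendance is perfect. The strength and hop indices use the uninvolved limb as reference. After a contralateral tear the reference limb is itself injured, and the index can rise without any gain in the operated knee.

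**Working it through.** **Inputs from the protocol article.** Evaluable number 72, dropout 10%, enrolled 80, power 80% and α 0.05 (*Sample size*). One baseline and three follow-up visits (*Procedure*, *Interventions*).

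**The plan's own figure.** 72 / (1 − 0.10) = 80. This reproduces exactly. I take 72 as given; how it was derived is a separate matter.

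**Complete cases under missed visits.** The article gives no per-visit rate, so the rate p is assumed. With independent misses at three follow-up visits and none at baseline, the complete fraction is (1 − p)³.

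- p = 5%: 0.95³ = 0.857; 80 × 0.857 = 68.6 complete; 14% lost.
- p = 10%: 0.90³ = 0.729; 80 × 0.729 = 58.3 complete; 27% lost.
- Break-even with the 10% allowance: (1 − p)³ = 0.90, so p = 1 − 0.90^(1/3) = 0.0345, about 3.5% per visit.

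**What this does to power.** Scale so that 72 complete cases (36 per arm) give 80% two-sided power in the normal approximation. The matching standardised difference is (1.960 + 0.842) × √(2/36) = 0.660. With n per arm, power is Φ(0.660 × √(n/2) − 1.960).

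- 68.6 complete (34.3 per arm): about 78%. Keeping 72 would need 72 / 0.857 = 84 enrolled.
- 58.3 complete (29.2 per arm): about 71%. Keeping 72 would need 72 / 0.729 = 98.8, so 99 enrolled.

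**The symmetry index after a contralateral tear.** Index = involved / uninvolved × 100. Take a patient at 80, the entry threshold, whose involved limb does not change. The index reaches 90, the return-to-sport threshold, once the uninvolved limb has fallen to 80/90 = 0.889 of its former strength, a loss of about 11%. The distance hops behave in the same way. The timed hop does too, because its ratio is inverted and a slower uninvolved limb also raises it.

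**The case against.** The strongest reply is that the article states no complete-case rule. It is a condensed account, and missing-data handling is commonly left to a full protocol or analysis plan that is not shown. That stands: a reader might infer that the plan deletes patients with a missed visit, but no such rule is written. The point concerns how the named method normally behaves, and that method is fixed in the text.

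Second, the article never says that all four visits enter one model, and it names ANCOVA for gait, the domain on which the sample size is based. A separate ANCOVA at each visit would keep the post-training result of a patient who misses year 2. This also stands as a possible reading. Against it, the sentence on the time factor is not limited to the clinical variables, and a within-subjects factor of time has no role in a visit-by-visit analysis.

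Third, the per-visit rates and their independence are assumptions. If dropout is permanent and totals 10% by year 2, exactly 72 complete cases remain, as planned. At 5% per visit the power loss is about two percentage points. Both remarks are correct and limit the size of the point.

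Finally, a reader might add the two second-injury ranges in the *Background* and conclude that the 10% allowance overlooks these injuries. The documents do not support that. A second injury is not a dropout, and re-injury is followed as an outcome. The ranges have no time horizon, nothing shows that they may be added or apply to this cohort, and what the 10% covers is not defined.

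**Conclusion.** The point holds as an improvement to the analysis method. It rests on the four visits entering one within-subjects model and on the classical method being run in its usual complete-case form. On that footing, the 10% allowance is enough only up to about 3.5% missed per follow-up visit. At the assumed 5% and 10%, about 69 and 58 of 80 remain, with power near 78% and 71%. The loss is small at the low end and material at the high end, and it is avoidable because the earlier data will have been collected.

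A reader might go further and infer that the randomised comparison is biased. That would need deletion to occur and the losses to be related to outcome in a way that differs by arm. The article expects more return to pre-injury level in the perturbation arm, but it does not predict differential loss.

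The issue with the symmetry indices is narrower. It affects only patients with a contralateral tear, and only at visits after it. The article gives no basis for counting them.

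**What to change.** Replace the repeated-measures ANOVA/ANCOVA by a linear mixed model on the post-baseline visits. Fixed effects: group, visit, group × visit, baseline value and gender (the stratification factor), with an unstructured covariance across visits. Analyse all randomised patients as randomised, use every observed visit, and report the group contrast at each visit.

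The mixed model does not settle how values measured after a contralateral tear are to be read, so add a sensitivity analysis at 1 and 2 years. For example, repeat the model with symmetry indices obtained after such a tear excluded, and show it beside the analysis of all observed values.

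The cost is analysis wording, standard software and one extra analysis, with no added patients or visits. The downside is that a missing-at-random assumption has to be stated. In the sensitivity analysis the same assumption also covers the excluded values, so that result describes the index as if the tear had not occurred.

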One year after surgery only 67% of patients have attempted some sort of training or sport activity; males are more likely than females to attempt full return to sport [34]. Individuals often do not return to their pre-injury activity level for a variety of reasons; fear of re-injury being a large contributing factor [35-37]. Patients in the medium to long term after surgery (two to seven years) that have returned to their pre-injury activity level were less likely to be fearful of re-injury during athletic participation than those that had not returned to their pre-injury level [37]. Females were more fearful with poor environmental conditions during athletic participation than their male counterparts [37].

Neuromuscular training, consisting of destabilizing perturbations to both the involved and uninvolved lower extremities, has been an effective means of enhancing functional outcomes after ACL injury compared to strength training [12,38]. Neuromuscular training programs such as perturbation training (PERT) [39] before surgery reduce gait asymmetries in female non-copers [18]. After surgery, non-copers who received pre-operative PERT demonstrated improved knee excursion symmetry during gait compared to patients who received strength training [12]. However, regardless of pre-operative intervention, aberrant movement patterns persisted up to two years after surgery [14]. Pilot data from our lab strongly suggests that utilizing this neuromuscular training program after surgery will be an effective means of improving both short term outcomes (6 months), when clearance to return to sport often occurs, and medium term outcomes (1-2 years) after surgery. Successful primary ACL prevention programs utilize a combination of balance, plyometric and strengthening exercises to decrease ACL injury risk. Similarly, our ACL-Specialized Post-Operative Return To Sports (ACL-SPORTS) Training will incorporate dynamic prevention exercises and quadriceps strengthening exercises that promote symmetrical joint loading and abate abnormal movement patterns. A post-operative intervention incorporating these elements with the addition of PERT may be effective in resolving residual impairments after surgery.

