### Exclusion criteria

Subjects will be excluded if: (i) not regular participants in level 1 or 2 activities (< 50 hrs/yr), (ii) > 10 months after ACLR, (iii) history of previous ACLR, (iv) history of serious ipsilateral or contralateral limb injury (i.e. Tibial fx), or (v) large osteochondral defect > 1 cm^2^ (Figure 1. CONSORT Flow Diagram of Study Protocol).

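### The ANOVA for the primary clinical variables could adjust for baseline value and weeks from surgery at almost no cost: a modest gain in precision, not a validity problem

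*Protocol article*

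**What the plan says.** The section Data and statistical analysis assigns an ANCOVA to the gait measures, without naming the covariate, and an ANOVA to the clinical variables. The factors are then given: "Training group randomization will be used as the between-subjects factor with a within-subjects factor of time". Time here means the test occasion, not time since surgery.

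The entry window is set in two places. Under Participants, eligible athletes "are ≥ 12 weeks after surgery, demonstrate ≥ 80% quadriceps strength index and minimal knee joint effusion". Under Exclusion criteria, patients are excluded if "> 10 months after ACLR". Randomization is stratified by gender only.

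The Interventions section ties the first two tests to the training block and fixes the last two at 1 and 2 years after surgery. Table 1 gives two sessions a week, so ten sessions take about 5 weeks.

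On recovery, the Background says of the IKDC 2000 that "scores continue to improve up to one year after surgery". The section Secondary outcome measures lists the IKDC 2000 as secondary. On movement patterns the Background says that "regardless of pre-operative intervention, aberrant movement patterns persisted up to two years after surgery".

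**The concern.** In the stated model for clinical variables, baseline is one level of the within-subject factor, so the treatment effect at 1 year is a difference in change from baseline. That baseline is measured anywhere between about week 12 and week 43, and the 1-year test comes at about week 52. If these measures are still improving in that period, early entrants have much natural gain ahead of them and late entrants little, whichever arm they are in.

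This spread goes into the error term. Any chance difference between arms in entry time also shifts the particular estimate obtained. Neither the stratification nor the stated clinical model takes up entry time, although it must be known for every patient in order to apply the eligibility limits. At stake is some precision in a trial of about 72 evaluable patients.

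**Working it through.** **Inputs from the article.** Entry from 12 weeks to 10 months (10 × 365.25 / 12 / 7 = 43.5 weeks); 72 evaluable patients, so 36 per arm; α = 0.05; effect size 0.3; 10% dropout.

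**The plan's own figure.** 72 / 0.90 = 80, which reproduces the enrolment target. The article does not state the metric of the 0.3. Read as Cohen's f it corresponds to d = 0.6, and 36 per arm then gives 71% power in a two-sided t-test. I use that only as a reference scale. How 72 was reached is a separate matter.

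**Recovery interval inside the change to 1 year.** 52.2 − 12 = about 40 weeks for the earliest entrant; 52.2 − 43.5 = about 9 weeks for the latest.

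**Chance imbalance.** Assume uniform entry over 12–43.5 weeks.
- SD of entry time = 31.5 / √12 = 9.09 weeks.
- SD of the difference between arm means = 9.09 × √(2/36) = 2.14 weeks.
- 95% range = ±1.96 × 2.14 = ±4.2 weeks.

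**Assumed recovery model.** Mean score m(t) = A(1 − exp(−t/τ)), with A = 15, 25 or 40 points and τ = 15 or 25 weeks. This gives a natural gain of about 6 to 20 points from week 12 to week 52. Between-patient SD is 6 and visit error SD is 6. None of these values is in the article.

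Let V be the variance of m(t) over entry time. It is 2.7 in the flattest case (A = 15, τ = 15) and 25.5 in the steepest (A = 40, τ = 25). In the change to 1 year the between-patient part cancels and the two visit errors leave 36 + 36 = 72.

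| Residual variance at 1 year | Formula | Flattest | Steepest |
|---|---|---|---|
| Unadjusted change | 72 + V | 74.7 | 97.5 |
| Baseline as covariate | 72 − 36²/(72 + V) | 54.7 | 58.7 |
| Baseline and entry time | 72 − 36²/72 | 54.0 | 54.0 |

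- Share of the unadjusted change explained by entry time: 2.7/74.7 = 0.036 to 25.5/97.5 = 0.26. Fitted as a straight line in weeks, 0.034 to 0.255.
- Further share once baseline is in the model: 1 − 54.0/54.7 = about 0.01 to 1 − 54.0/58.7 = 0.08. Fitted linearly, 0.011 to 0.077.
- Change to the post-training test, taken 7 weeks after baseline: 0.003 to 0.033.
- Share of the 1-year score itself: zero, because every patient is then at the same time from surgery.

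**Power,** two-sided, 36 per arm, d = 0.6 / √(1 − R²):
- R² = 0: 71%.
- R² = 0.011 to 0.077 (baseline already in the model): 71% to 74%.
- R² = 0.034 to 0.255 (unadjusted change): 72% to 83%.

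**Type I error.** Null simulations (4,000 trials per setting, entry-time R² of 0.05, 0.10 and 0.25) gave rejection rates of 0.042 to 0.052 without entry time in the model, so the test stays at its nominal level.

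**The case against.** Five arguments stand on the other side.

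- **Gait.** An ANCOVA has at least one covariate, and the article does not say which. A reader might infer that entry time is omitted from all primary analyses. The text does not support that, and a journal article may leave a covariate list to the full protocol.
- **Recovery with time.** A reader might infer that the article shows time from surgery to drive recovery in the primary outcomes. It does not. The stated support is the IKDC 2000, a secondary outcome; for movement patterns the article reports persistence to two years. That entry time is prognostic for the clinical measures is likely, not documented.
- **Functional gating.** The Discussion says "Our criterion to implement training is based on an array of evidence based clinical measures rather than time based measures". Entry time is then partly the time taken to reach a functional threshold, which the assumed curves ignore. The link with baseline score may be weaker than modelled, though late entrants may also include slower recoverers.
- **Source of the gain.** The larger figures belong to unadjusted change scores. Under the assumed curves most of the available gain comes from using baseline as a covariate, and entry time then adds little. The planned effect size also rests on sagittal gait variables, so its use for clinical scores is illustrative.
- **Imbalance.** A reader might infer bias from uncorrected imbalance. Chance imbalance is already covered by the 5% error rate, and imbalance visible at baseline is removed by the group-by-time contrast.

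It could also be said that entry time cannot matter at the 1- and 2-year tests because all patients are then equally far from surgery. That is true of the scores but not of the change from baseline, which is what the stated model compares.

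**Conclusion.** The point holds as a low-severity, nearly free improvement, confined to the primary clinical variables. The stated ANOVA with group and visit leaves some precision unused at the 1-year comparison and almost none at the post-training test. With baseline adjusted for, entry time is worth about 1–8% of the 1-year variance, or at most about 3 points of power from 71%.

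These figures rest on uniform entry, on the assumed curves and SDs, and on reading 0.3 as Cohen's f. The true size is unknown, because the article gives no slope. The plan is valid as it stands: no bias and no inflation of type I error follows from leaving entry time out.

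**What to change.** In Data and statistical analysis, replace the ANOVA for the clinical variables with a prespecified repeated-measures model of the follow-up scores. It should contain group, visit and their interaction, the baseline value of the outcome, and weeks from surgery to the baseline test as a continuous covariate with its visit interaction. Report the distribution of weeks from surgery by arm.

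The cost is a sentence or two and one to three degrees of freedom for the entry-time terms. The value is already needed for eligibility, so no new data or patients are required. Prespecifying it also avoids choosing covariates after seeing an imbalance. For the gait ANCOVA, naming the covariate would settle the question; no error is shown there.
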